**Figure 1 figure1:**
[figure not shown]
Study process flowchart. CBT: cognitive behavioral therapy; CG: complaining good; CP: complaining poor; NG: noncomplaining good; NP: noncomplaining poor; SOL: sleep onset latency; WASO: wake-after-sleep onset.

### Description of Intervention

There are a variety of web-based CBT-I courses, mostly developed in the United Kingdom or the United States. One exception is the “This Way Up—Managing Insomnia” program [55,56]. This treatment course was created by a team of clinical psychologists and psychiatrists at the Clinical Research Unit for Anxiety and Depression, which is run by the University of New South Wales and St Vincent’s Hospital in Sydney. The free self-help program consists of 4 lessons in a comic-based format. Lesson 1 provides background knowledge about sleep and insomnia and which factors are conducive to good sleep and which ones are related to insomnia (sleep hygiene). Lessons 2 and 3 address the management of thoughts and behaviors that interfere with sleep (sleep restriction, stimulus control, and cognitive therapy). The sleep restriction protocol aims at decreasing nighttime awakenings by limiting the time a person spends in bed [57]. Initially, the prescribed time in bed corresponds with the average total sleep time as measured in the week prior to initiating the sleep restriction protocol, with a minimum time in bed of 5.5 hours. Time in bed is then gradually increased until the amount of nighttime sleep achieved is sufficient for individual requirements. Lesson 4 focuses on relaxation techniques. The program cannot be individually tailored to the patient’s specific sleep difficulties but provides broad topic coverage of the most common factors present in insomnia (eg, waking too early), and program participants are advised that not all themes covered may be relevant to their circumstances.

Each lesson takes about 20 minutes to complete, with additional compulsory homework. A unit only registers as completed once the homework has been downloaded. It is recommended that a user completes 1 lesson every 1-2 weeks. However, the system will not grant access for less than 5 days between modules. Reminders are emailed or sent by text message automatically once a new session becomes available, and there is also the option to set a web-based appointment for the next course module. In addition to the course unit and homework, participants are required to complete a sleep diary. Upon completion of the course, an extra 12 months’ access is made available for additional practice. The program is available only to individuals who live in Australia.

The program’s easy-to-access platform makes it suitable even for individuals with low eHealth literacy. This could be important when providing web-based CBT-I to older populations, even though older adults are increasingly familiar with using the internet and social media. A recent report exploring the attitudes and behaviors of adults aged 70 years and older pointed out that 99% of individuals have searched for information on the internet, 65% of them post on or read from social media, and 82% of them who are on social media use Facebook [46].

Participants with moderate to extremely severe total scores on any scale of the DASS-21 (Depression, Anxiety, and Stress Scale-21) will receive a letter outlining the results and will be encouraged to discuss these with their health care professionals. This is considered an advisable measure of duty of care. However, while the DASS-21 measures the emotional states of anxiety, stress, and depression over the previous week, it is based on a dimensional rather than a categorical conception of disorder and should not be used as a diagnostic tool [58]. Participants with ongoing or severe insomnia, stress, anxiety, or depression symptoms will be advised to contact the university’s Psychological Services Centre or community services such as Lifeline.

Consideration will also be given to the delivery of a sleep restriction module as part of the web-based CBT-I. Any contraindications to CBT-I usually arise from the use of the sleep restriction element and occur when an individual has epilepsy, bipolar disorder, or is at high risk of falling, and can also exacerbate symptoms in those with excessive daytime sleepiness, for example, in individuals with sleep apnea [59]. Participants will be screened for obstructive sleep apnea risk using the STOP-Bang questionnaire and will be asked if they have ever been diagnosed with epilepsy or severe psychiatric (eg, bipolar disorder) or cognitive impairment (eg, mild cognitive impairment). Participants will also be questioned about their fall risk, including queries about whether they have had a fall in the past year, feel unsteady when standing or walking, or if they are worried about falling. Participants with epilepsy, bipolar disorder, cognitive impairment, a sleep apnea diagnosis, or a high fall risk will be excluded from the study. Individuals with any other psychiatric disorder (eg, borderline personality disorder) will be excluded depending on their active symptomatology and current management of the condition, following consultation with the clinical psychologist on the research team. Cognitive disorders and personality disorders will be assessed through self-report.

### Statistical Analysis

An a priori power analysis using the program G*Power was performed to assess whether the study will have enough power to detect significant differences in sleep outcomes between the study groups [60]. We calculated that a sample size of 40 would be sufficient to detect this size effect. In order to account for attrition rates and missing data, a minimum of 60 participants will be recruited for the study.

Since sleep complaint status (sleep problem, eg, initial insomnia, for a minimum of 6 months) is used to classify participants as complaining or noncomplaining sleepers, multivariate ANOVA will be conducted separately to examine subjective and objective sleep quality for the 4 sleep groups. The multivariate ANOVA enables the analysis of multiple continuous dependent variables simultaneously (eg, sleep onset latency, wake-after-sleep onset, total sleep time, and the number of nighttime awakenings). In addition, a mediation analysis will be performed to determine whether sleep improvements following web-based CBT-I are the result of changes in sleep-related beliefs or other factors in older adults living in the community. Mediation analysis will be carried out using the bootstrapping method in the Hayes Process Macro for mediation, moderation, and conditional analysis for SPSS (version 28.0; IBM Corp) [61,62].

Actigraphy measures will be scored using the Cole-Kripke algorithm, which is suitable for use with older populations [63] and using ActiLife software (ActiLife 6 software, Version 6.13.1, ActiGraph). The autoscored data will be manually compared with the sleep diary to determine any incongruence between the actigraph measurements and the sleep diary.

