The concurrent measurement of objective and subjective sleep quality will be used to determine the prevalence of individuals with asynchronous sleep patterns and sleep appraisal in this sample (phase 1). Phase 2 will assess the impact of a web-based CBT-I program on the sleep outcomes of individuals with synchronous sleep patterns and sleep appraisal and those with asynchronous sleep patterns and sleep appraisal. It is anticipated that complaining good sleepers and complaining poor sleepers will show improved sleep outcomes following CBT-I, compared with noncomplaining good and poor sleepers. We further hypothesize that individuals with a sleep complaint but without poor sleep quality (complaining good sleepers) experience higher levels of dysfunctional sleep cognitions and distress than persons with poor sleep in the absence of a sleep complaint (noncomplaining poor sleepers). We expect that additional factors such as hyperarousal [35], sleep effort [36], sleep-related self-efficacy [37], sleep locus of control [38], sleep-related behaviors [39], and chronotype [40] mediate the relationship between web-based CBT-I and sleep outcomes in older adults; therefore, these processes will also be examined.

Since our planned study is likely to generate a considerable amount of data, we aim to reduce publication bias and improve the reproducibility of our research by publishing this research protocol.

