Participants will wear an actigraph and complete a sleep diary over 96 hours (72 hours plus an additional 24 hours to account for nonadherence wear time). Actigraphic sleep assessment will assess sleep onset latency, wake-after-sleep onset, total sleep time, and the number of nighttime awakenings. The Actigraph model wGT3X-BT activity monitor (ActiGraph) will be used. Actigraphy has been recognized by the American Academy of Sleep Medicine as an appropriate method for assessing sleep. However, when compared with polysomnography, actigraphy has lower accuracy in detecting wake periods; especially in individuals with poor sleep quality [50]. The actigraphy data will be manually scored along with a sleep diary. This process was recommended by Boyne et al [51] to optimize agreement with polysomnography-measured sleep-wake. Additionally, the Choi algorithm will be used to differentiate between wear and nonwear times, which more accurately estimates time spent sedentary than other algorithms [52]. The sleep diary is a modified version of the Consensus Sleep Diary [53], which, in addition to the questions covered by the Consensus Sleep Diary, records the total duration of all daytime naps, how many times the study participant got up during the night, what time they had planned to wake up at, and whether they took any sleep medication.

Participants will be grouped into 4 sleep groups: noncomplaining good sleepers, complaining good sleepers, noncomplaining poor sleepers, and complaining poor sleepers. Participants will be grouped based on their actigraphy results and sleep complaint status (complaining versus noncomplaining sleepers), with participants appraised as poor sleepers if their sleep onset latency or wake-after-sleep onset is ≥31 minutes, 3 times or more during the recording period (as per actigraph recording). A participant will be considered a complaining sleeper if they report having had a sleep problem (eg, trouble falling asleep) for a minimum of 6 months at baseline data collection [5,54].

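### The four-group MANOVA does not test the complaint prediction or the coupled-versus-uncoupled aim; each needs its own contrast

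*Protocol article*

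**What the plan says.** The protocol article poses three distinct group questions.

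- **Complaint (Introduction).** It anticipates that "complaining good sleepers and complaining poor sleepers will show improved sleep outcomes following CBT-I, compared with noncomplaining good and poor sleepers".
- **Uncoupling (Abstract, Objective and Methods).** Phase 2 compares the effect of web-based CBT-I in people whose sleep pattern and appraisal disagree with its effect in people whose pattern and appraisal agree.
- **Cognitions (Introduction).** Complaining good sleepers are expected to "experience higher levels of dysfunctional sleep cognitions and distress than persons with poor sleep in the absence of a sleep complaint".

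The Statistical Analysis section names one between-group analysis: "multivariate ANOVA will be conducted separately to examine subjective and objective sleep quality for the 4 sleep groups". The example outcomes are "sleep onset latency, wake-after-sleep onset, total sleep time, and the number of nighttime awakenings". The section does not say whether the outcomes are baseline values, post-treatment values or changes. The other named analysis is different in kind: "a mediation analysis will be performed to determine whether sleep improvements following web-based CBT-I are the result of changes in sleep-related beliefs". It asks why sleep improves, not which groups improve more.

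The Design section classes participants as "poor sleepers if their sleep onset latency or wake-after-sleep onset is ≥31 minutes, 3 times or more during the recording period", as recorded by actigraphy.

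**The concern.** A MANOVA over four groups asks whether any group differs from any other on any outcome, in any direction. None of the three questions is that broad. A significant result therefore cannot be read as support for the complaint prediction, because a difference between good and poor sleepers alone can produce it. A non-significant result is weak evidence against the prediction, because the test spreads its sensitivity over three contrasts when the prediction concerns one.

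The problem is sharper for the objective outcomes. Sleep onset latency and wake-after-sleep onset define the good/poor split and are also listed as outcomes. At baseline, a good/poor difference on them is built in by the grouping. After treatment, regression to the mean in groups selected for high values could carry a good/poor difference into the change scores, whatever complaint does.

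**Working it through.** **1. The nulls side by side.** Write NG, CG, NP and CP for the mean vectors of noncomplaining good, complaining good, noncomplaining poor and complaining poor sleepers.

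- Four-group MANOVA: NG = CG = NP = CP. This has 3 df per outcome, so 3 x 4 = 12 hypothesis df with the four listed outcomes.
- Complaint prediction: (CG + CP)/2 - (NG + NP)/2 = 0. This is 1 df per outcome, the complaint main effect of a 2 x 2 layout.
- Uncoupled versus coupled: (CG + NP)/2 - (NG + CP)/2 = 0. This is 1 df per outcome and is the 2 x 2 interaction up to a constant, since CP - CG - NP + NG equals -2 times it.
- Cognition hypothesis: CG - NP = 0, on belief and distress measures rather than sleep outcomes.

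**2. The plan's own figure.** The article says: "We calculated that a sample size of 40 would be sufficient to detect this size effect". The effect size, alpha, power and test are not shown, so 40 cannot be reproduced. For scale, take one outcome, equal groups, alpha 0.05 and 80% power, with d = 2f. A four-group ANOVA with N = 40 then detects f = 0.55 (d = 1.10), and the complaint contrast f = 0.46 (d = 0.91). With N = 60 the detectable effects are d = 0.88 and d = 0.74.

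**3. Assumptions for the comparison.** N = 60 is the recruitment target, and p = 4 outcomes are listed. Assumed: common correlation 0.3, alpha 0.05, and the same shift d on every outcome. Two splits (NG/CG/NP/CP) are used: 15/15/15/15 and 20/14/6/20. The second puts (14 + 6)/60 = 33% in the uncoupled groups, inside the 25%-35% quoted in the Introduction.

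**4. Power of the complaint contrast (Hotelling T2).**

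- Squared distance: d² x p/(1 + (p - 1) x 0.3) = d² x 4/1.9 = 2.105 d². This is 0.526 at d = 0.5 and 1.347 at d = 0.8.
- Contrast variance factor v, the sum of c²/n with c = ±1/2. Equal split: 4 x 0.25/15 = 0.0667. Uneven split: 0.25 x (1/20 + 1/14 + 1/6 + 1/20) = 0.0845.
- Noncentrality = squared distance / v. At d = 0.5 it is 7.89 (equal) and 6.23 (uneven). At d = 0.8 it is 20.21 and 15.94.
- Referred to F with 4 and 56 - 4 + 1 = 53 df (critical value 2.546), power is 56% and 45% at d = 0.5, and 95% and 88% at d = 0.8.

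**5. Four-group test (Pillai).** Rejection rates come from 20,000 simulated trials per scenario. Cells give equal split / uneven split. Contrast power in the last two rows is from step 4; the simulation agrees with it to within one point.

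| True state | Four-group test | Complaint contrast |
|---|---|---|
| No differences | 4% / 4% | 5% / 5% |
| Good/poor 0.5 SD only | 31% / 31% | 5% / 5% |
| Good/poor 0.8 SD only | 77% / 76% | 5% / 5% |
| Complaint 0.5 SD only | 32% / 31% | 56% / 45% |
| Complaint 0.8 SD only | 76% / 75% | 95% / 88% |

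If only two of the four outcomes differ between good and poor sleepers, by 1 SD (as latency and wake time might), the four-group test rejects 92% of the time with equal groups at N = 60.

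**6. One outcome only, equal groups, N = 60.** Power of the four-group ANOVA against the contrast is 32% against 48% at 0.5 SD, and 71% against 86% at 0.8 SD.

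**The case against.** The strongest reply is that the MANOVA sentence describes phase 1. It speaks of examining sleep quality in the four groups, which matches the phase 1 objective, and it mentions neither treatment nor change. On that reading it is not a mismatched test of improvement. This is possible, but the phase 2 group prediction is then left without any matching test in the article.

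A second reply is that the protocol does not say the MANOVA stands alone. The groups are built by crossing two binary attributes, and a 2 x 2 layout or planned contrasts may sit in an analysis plan that is not shown. This stands, so the point is not that contrasts are absent. It is that the test the article does name does not isolate what the article predicts.

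Several stronger readings are tempting and are not supported:

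- **That the other degrees of freedom in the four-group test are of no interest.** The uncoupled-versus-coupled comparison is a stated aim and is the 2 x 2 interaction. The trouble is that the joint test cannot tell the questions apart.
- **That the sleep-outcome MANOVA is the test of the cognition hypothesis.** The article never says so.
- **That the test always rejects for the wrong reason, or always rejects less often.** It does the first only if the groups differ in some way other than complaint. When complaint and poor sleep each add 0.5 SD, it rejects more often than the complaint contrast (64% against 56% with equal groups, 78% against 45% with the uneven split), but that is rejection of a broader null.
- **That a multivariate contrast settles direction.** It is as non-directional as the MANOVA.

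**Conclusion.** The point holds in a limited form. The named four-group test has a different null from the complaint prediction and from the uncoupled-versus-coupled aim, so its p-value supports neither. Under the assumptions in steps 3 to 5, a good/poor difference alone makes it significant in about 31% of trials at 0.5 SD and 76-77% at 0.8 SD. If complaint alone matters, it gives up 14 to 24 points of power at 0.5 SD and 13 to 19 points at 0.8 SD. The difference in nulls follows from the text. The sizes rest on assumed effects, correlation and splits, because the article gives none, and the power loss applies to the pattern in which complaint, not sleep quality, drives improvement. That baseline latency and wake time differ between good and poor sleepers follows from the Design section itself. Nothing here shows that any reported result is wrong.

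**What to change.** In Statistical Analysis, state which phase the MANOVA serves and analyse the same outcomes with a 2 x 2 model, complaint by sleep quality, with equal cell weights because the cells will be uneven.

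- For phase 2, use the complaint main-effect contrast on improvement as the test of the Introduction's prediction.
- Use the complaint by quality interaction on improvement as the test of the uncoupled-versus-coupled aim.
- Test the cognition hypothesis with a complaining-good versus noncomplaining-poor contrast on the DBAS-16 and on a named distress measure. The DASS-21 appears in Description of Intervention but is not tied to this hypothesis.
- Report signed estimates with 95% confidence intervals for each outcome, and judge direction from these.
- Keep the four-group test as descriptive, and do not cite its p-value in support of any of these hypotheses.

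The Results section says analysis of both phases is finished. Unless an earlier dated analysis plan already contains these contrasts, label them as specified after data collection. The cost is some wording and a few lines of contrast syntax on existing data, with no further participants. The downsides are that the four-group test loses confirmatory standing and that several contrasts are tested in place of one, so the plan should say which is the principal one.

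### The phase 1 objective-sleep MANOVA compares the 4 groups on the same baseline actigraphic variables that define its good/poor half, so its omnibus test is largely circular

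*Protocol article*

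**What the plan says.** Grouping (Protocol article, Design). "Participants will be grouped based on their actigraphy results and sleep complaint status". On the actigraphic axis the rule is "participants appraised as poor sleepers if their sleep onset latency or wake-after-sleep onset is ≥31 minutes, 3 times or more during the recording period". On the other axis, "A participant will be considered a complaining sleeper if they report having had a sleep problem" that has lasted at least 6 months at baseline.

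Measurement (Design). "Participants will wear an actigraph and complete a sleep diary over 96 hours", which is the only baseline recording described. "Actigraphic sleep assessment will assess sleep onset latency, wake-after-sleep onset, total sleep time, and the number of nighttime awakenings".

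Analysis (Statistical Analysis). "multivariate ANOVA will be conducted separately to examine subjective and objective sleep quality for the 4 sleep groups". The dependent variables are illustrated as "eg, sleep onset latency, wake-after-sleep onset, total sleep time, and the number of nighttime awakenings", the same four that the Design section lists for actigraphy. The reason given for running separate MANOVAs refers only to complaint status; the actigraphic classification is not mentioned.

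Aims (Abstract and Introduction). Phase 1 assesses objective and subjective sleep and the prevalence of asynchronous sleepers. The stated objective compares sleep quality between people whose sleep pattern and appraisal agree and people in whom they do not.

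**The concern.** Whether a participant is a good or a poor sleeper is fixed entirely by nightly SOL and WASO at baseline. If the four groups are then tested for equal mean SOL and WASO over the same nights, the good and poor groups differ because they were sorted to differ. Running the objective and subjective MANOVAs separately does not help, because the actigraphic factor remains inside the actigraphic MANOVA.

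What is at stake is how the phase 1 objective-sleep result is read. A small omnibus p-value could be reported as evidence that the four types of sleeper have different objective sleep, when most or all of it may restate the classification rule. The informative questions are whether complainers differ in measured sleep from non-complainers of the same actigraphic class, and whether synchronous differ from asynchronous sleepers (the interaction in a 2x2 layout). A one-way test over four groups isolates neither.

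**Working it through.** **The plan's own figure.** The only number attached to the group comparison is N=40 from G\*Power, raised to 60 for attrition and missing data; 65 were recruited. Effect size, alpha, power and test are not stated, so 40 cannot be reproduced. For orientation, with a one-way four-group ANOVA and an assumed alpha of 0.05, N=40 would correspond to Cohen's f of about 0.55 (80% power) to 0.69 (95% power). The argument below does not depend on this.

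**Step 1: from the text alone.** Let D be the number of recorded nights with SOL or WASO at or above 31 minutes. The recording covers 96/24 = 4 nights, and a participant is poor if D ≥ 3. The dependent variables include SOL and WASO from those same nights. Anyone with D ≥ 3 has at least three nights with a high value, and anyone classed as good has at most two. Mean SOL or WASO is therefore pushed up in the poor groups and down in the good groups, even if every person has the same underlying sleep and D varies only by chance. The null hypothesis of equal means is false by the rule.

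**Step 2: size.** The documents give no SOL or WASO distribution, so these inputs are assumptions: 4 nights; log-normal nightly values; median SOL 12 min; median WASO 25 to 45 min; log-SD 0.6; complaint status assigned at random (50%); total sleep time (TST) and awakenings unrelated to group; Pillai trace at 5%. ICC is the between-person share of night-to-night variance (on the log scale); ICC 0 means no stable differences between persons. With 600 runs per setting, the Monte Carlo standard error is at most √(0.5 × 0.5 / 600) = 0.020, or 2 percentage points.

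Rejection rate of the four-group test at ICC 0 (nominal 5%):

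| N | median WASO 25-35 min | median WASO 45 min | range over all assumed inputs tried |
|---|---|---|---|
| 40 | 58-65% | 30% | 26-65% |
| 60 | 85-88% | 52% | 48-88% |
| 65 | 86-93% | 58% | 56-93% |

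The last column also covers further simulations of the same design, including one with median SOL 15 min, median WASO 30 min and log-SD 0.7 (61% at N=40, 88% at N=60).

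**Step 3: where the excess comes from.**
- Classify on one recording and test on another (N=60, median WASO 30, ICC 0): rejection falls from 88% to 4%.
- Leave SOL and WASO out of the dependent variables: 3-7%. This holds because TST and awakenings were simulated as unrelated to group; in real data they may correlate with SOL and WASO.
- Test complaint status alone: 3-6%. The excess therefore lies on the good/poor axis.

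**Step 4: when people really differ.** At N=60 and median WASO 30, the same-recording test rejects in about 100% of runs at ICC 0.3 and at ICC 0.5. With separate recordings it still rejects in 60% and 93%. The excess due to re-using the same nights is thus about 100 − 60 = 40 points and 100 − 93 = 7 points; the rest reflects real stable differences.

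**The case against.** Several points on the other side have force.

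*The variable list is only an example.* It is introduced by 'eg', explains what a MANOVA does, and does not say baseline or actigraphic. But SOL and WASO head the list, the Design section gives the same four as the actigraphic measures, and nothing excludes the two defining variables. An unseen analysis plan could add contrasts, but the article itself states both the grouping rule and a test that overlaps with it.

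*Significance is not guaranteed.* This stands. A reader might infer that the test must come out significant. Under the assumptions above it can reject in as few as 26% of trials (N=40, median WASO 45 min). What the grouping rule settles is that the null is false, not that each trial will reject it.

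*Near-certain rejection at higher ICC is not all artefact.* This also stands. If persons differ stably in sleep, much of the rejection is correct, as Step 4 shows. The ICC 0 figures are the ones that isolate the circularity.

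*The subjective MANOVA.* A reader might infer that it is circular in the same way because complaint is self-reported. The documents do not support this. Complaint status is a reported problem of at least 6 months; it is not calculated from the Insomnia Severity Index (past 2 weeks) or the Pittsburgh Sleep Quality Index (past month). The constructs overlap, which deserves a remark, but one is not a function of the other.

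*The rest of the trial.* A reader might infer that phase 1 as a whole cannot answer its question. It can in part: the prevalence of asynchronous sleepers is a cross-classification that needs no MANOVA, and the hypotheses in the Introduction concern response to treatment, dysfunctional cognitions and mediators, none of which is a baseline good/poor difference in SOL or WASO. Post-treatment actigraphy is a separate recording.

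**Conclusion.** The concern holds for one analysis: the phase 1 omnibus MANOVA of objective sleep over the four groups, as far as it includes SOL and WASO. That the null is false by the grouping rule follows from the text and needs no outside figure. The size rests on assumed distributions: with no stable between-person differences and random complaint status, rejection is roughly 26-65% at N=40, 48-88% at N=60 and 56-93% at N=65, against 5%. At higher ICC the rate rises further, but part of it then reflects real differences. A significant result would therefore say little about how complaint relates to measured sleep.

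The documents do not support extending this to the subjective-sleep MANOVA, the prevalence estimate, the complaint contrasts or the post-treatment actigraphy.

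**What to change.** For baseline actigraphic outcomes:

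1. Replace the one-way four-group omnibus test by a 2x2 model with complaint (yes/no) and actigraphic class (good/poor).
2. Base inference on the complaint effect within good sleepers and within poor sleepers. State that these comparisons are made over a restricted range of SOL and WASO, so a small difference within a class does not show that complaint and measured sleep are unrelated overall.
3. Report good/poor differences in SOL and WASO as a description of the grouping, without a p-value.
4. Attach a caution to good/poor differences in TST and awakenings, because they may correlate with SOL and WASO from the same nights.

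Leave the subjective-sleep MANOVA as planned, with a sentence noting that complaint status is itself self-reported and overlaps in construct with the Insomnia Severity Index and the Pittsburgh Sleep Quality Index.

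The article reports that the phase 1 analysis is finished and its results submitted, so the cost is a rerun on data already held and a change of wording in the analysis section and the phase 1 report. No new data are needed.
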